### Recruitment {15}

Participants will be recruited primarily in the outpatient clinic as well as the endoscopic centre of Liaocheng People’s Hospital by the investigators. In addition, we have a dedicated phone number to answer any inquiries about participation in the study. It is estimated that there are 100–150 recently diagnosed *H. pylori* infection patients visiting our outpatient clinic each month. The investigators will inform eligible patients about the study and ensure that they understand the implications of participating in it. Patients will be asked to give consent to participate in the study by signing an informed consent form.

## Assignment of interventions: allocation

### Sequence generation {16a}

For random allocation, an independent research assistant will generate a randomised number table using IBM SPSS Statistics for Windows software version 22.0 (IBM Corp., Armonk, NY, USA) ahead of the study.

### Concealment mechanism {16b}

The randomised number table will be sealed in an opaque envelope and retained by the independent research assistant.

### Implementation {16c}

Once the investigators obtain informed consent from a participant, they will call the independent research assistant to obtain the allocated regimen for that participant.

## Assignment of interventions: blinding

### Who will be blinded {17a}

As this is an open-label study, it is impossible to blind the participants or investigators. However, the data collectors and data analysts will remain blinded to treatment allocation throughout the study. For AEs and compliance, a data collection form (Additional File 2) concealing the allocation information will be used, and data collectors are not allowed to ask participants about their treatment regimen. The allocation information will also be concealed from the dataset that will be distributed to the data analysts.

### Procedure for unblinding if needed {17b}

Not applicable because it is not possible to blind the participants or investigators.

## Data collection and management

### Plans for assessment and collection of outcomes {18a}

Sociodemographic and baseline information (including name, sex, age, contact information, and past medical history) will be collected during screening. The success of *H. pylori* eradication will be assessed using 13C-UBT 4 weeks after therapy completion. Before getting the 13C-UBT done, participants will not be allowed to use any PPIs or antibiotics for 2 weeks and 30 days, respectively. Considering the impact of the COVID-19 pandemic, we require the 13C-UBT to be done at most 8 weeks after the completion of therapy. The information on AEs and compliance throughout the study will be collected via telephone and recorded using the data collection form (Additional file 2) 3 days after the completion of therapy. Study drug compliance will be based on the number of days of drug administration. Because 10-day therapy regimens can achieve good eradication rates [28, 29], 10 or more days will be considered good compliance and less than 10 days bad compliance. Data will be collected by two dedicated data collectors who will be trained in collecting the information in a uniform, reproducible manner, and the quality of the data will be supervised by the principal investigator.

### *P*lans to promote participant retention and complete follow-up {18b}

Investigators will provide periodic communications with participants via telephone and WeChat. They will use methods to improve participant retention, such as reminders for taking the study drug, and scheduling appointments for the 13C-UBT.

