### Strategies to improve adherence to interventions {11c}

Face-to-face adherence reminder sessions will take place during the initial drug dispensing. Sessions will cover the importance of participants completing treatment regimens and calling investigators if experiencing problems that may be related to study drugs. Moreover, participants will receive instructions on taking study pills (dose, timing, storage) and what to do in the event of a missed dose. Furthermore, participants will receive a compliance reminder phone call 1 week after the start of treatment, and a 13C-UBT test reminder call 4 weeks after the end of treatment.

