### Outcomes {12}

The primary outcome of the study is the proportion of participants with successful *H. pylori* eradication. This will be determined according to the results of 13C-UBTs performed at least 4 weeks after the end of the first-line treatment period between the SGT and ET groups.

The secondary outcomes: The rescue treatment and the overall eradication rates in the SGT and ET groups. The eradication rate of HDDT for the clarithromycin resistance group and the empirical BQT failure group. Frequency of AEs and the rate of compliance between the SGT and ET groups.

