### Methods in analysis to handle protocol non-adherence and any statistical methods to handle missing data {20c}

The primary and secondary outcomes will be evaluated using ITT, mITT, and PP analyses. Participants who have not undergone a re-examined 13C-UBT will be considered as treatment failures, i.e., ‘not eradicated,’ in the statistical analysis. Strategies will be implemented to maximise follow-up, improve adherence, and prevent missing data. We will report the reasons for non-adherence for each randomisation group and compare the reasons qualitatively.

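### Breath-test booking is assigned to investigators who know the allocation, while an untested participant counts as a failure: an avoidable route for bias into the ITT and mITT primary result

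*Protocol article*

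**What the plan says.** All references are to the protocol article.

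- **Outcomes {12}:** "The primary outcome of the study is the proportion of participants with successful *H. pylori* eradication", judged by the 13C urea breath test (UBT) at least 4 weeks after first-line treatment. Section {18a} sets an upper limit of 8 weeks.
- **Who will be blinded {17a}:** "As this is an open-label study, it is impossible to blind the participants or investigators". By contrast, "the data collectors and data analysts will remain blinded to treatment allocation throughout the study". The collectors use a form that hides the allocation and may not ask which regimen was taken.
- **Retention {18b}:** "Investigators will provide periodic communications with participants via telephone and WeChat". The methods named are "reminders for taking the study drug, and scheduling appointments for the 13C-UBT". No number of contacts, cap or rule of equal contact is given.
- **Adherence {11c}:** one compliance call a week into treatment and "a 13C-UBT test reminder call 4 weeks after the end of treatment". The caller is not named.
- **Missing data {20c}, repeated in {20a}:** "Participants who have not undergone a re-examined 13C-UBT will be considered as treatment failures".
- **Data collection {18a}:** the collectors obtain adverse events and compliance by telephone 3 days after therapy ends.

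**The concern.** Under the missing-equals-failure rule, a participant scores as a success only by being cured and also attending the test. The task that most directly affects attendance, which is booking the test and following up those who have not come, is given to staff who know the arm. The protocol takes care to blind the collection of adverse events and compliance, but leaves the booking of the primary-outcome test outside that protection.

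The UBT is an objective measurement, which protects the reading of the result. It does not protect against a difference in who gets tested. If follow-up effort differed by arm, for whatever reason, ITT and mITT could show a difference between regimens that perform equally, or hide a real one.

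**Working it through.** **Inputs from the protocol article.** Sample size {14}: 90% versus 80% eradication, two-sided alpha 0.05, power 80%, 20% dropout, target 500 (250 per arm). Sections {20a} and {20c}: no repeat UBT counts as failure.

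**Inputs that are assumptions.** The same true eradication in both arms, 85% (range 80% to 90%). Attendance of 85% versus 80%, and of 90% versus 80%. Attendance unrelated to cure within an arm. The document gives no attendance by arm.

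**Step 1: the plan's own figure.** n = (1.960 + 0.842)² × (0.90 × 0.10 + 0.80 × 0.20) / 0.10² = 7.849 × 0.25 / 0.01 = 196.2, so 197 per arm. With dropout, 197 / 0.80 = 246.25, so 247 per arm and 494 in all. Both figures reproduce.

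**Step 2: what the rule does.** Observed rate = true rate × attendance. At 85% true eradication, each point of attendance gap moves the observed difference by 0.85 points.

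**Step 3: attendance 85% versus 80%, no true difference.**
- Rates: 0.85 × 0.85 = 0.7225 and 0.85 × 0.80 = 0.680. Difference 4.25 points.
- SE = √(0.7225 × 0.2775/250 + 0.68 × 0.32/250) = 0.0409; z = 0.0425/0.0409 = 1.04.
- Chance of significance in favour of the better-attending arm: P(Z > 1.96 − 1.04) ≈ 0.18, against a nominal 0.025 in that direction.
- A 5-point gap is 0.05 × 250 = 12.5, so 12 or 13 participants in one arm.

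**Step 4: attendance 90% versus 80%, no true difference.**
- Rates: 0.85 × 0.90 = 0.765 and 0.680. Difference 8.5 points.
- SE = √(0.765 × 0.235/250 + 0.68 × 0.32/250) = 0.0399; z = 2.13; P(Z > 1.96 − 2.13) ≈ 0.57.

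**Step 5: range.** With true eradication from 80% to 90% in both arms, the 5-point gap gives 4.0 to 4.5 points and about 16% to 21%. The 10-point gap gives 8.0 to 9.0 points and about 48% to 66%. An attendance gap of 0.10/0.90 = 11.1 to 0.10/0.80 = 12.5 points would by itself produce the planned 10-point effect.

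**Step 6: the other direction, and the equal case.** With true rates of 90% and 80%, attendance of 80% in the susceptibility-guided arm and 90% in the empirical arm gives 0.90 × 0.80 = 0.72 and 0.80 × 0.90 = 0.72, so the real effect disappears. With equal attendance and equal true rates, the two-sided error rate stays at 5%.

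These are normal approximations. The planned Miettinen & Nurminen interval will differ slightly.

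**The case against.** The strongest reply is that the retention section may be no more than a general restatement of the two timed calls in the adherence section, since its two examples closely match them. Both sections speak of participants without distinguishing arms, and call scripts and attempt limits are details that an article may leave to the full protocol. This stands in part: not all contact is open-ended, and the absence of a script is not itself the point. The point is a stated assignment. Booking is given to investigators, and a single reminder at 4 weeks, from an unnamed caller, does not govern the four weeks that remain before the deadline.

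A reader might infer that the susceptibility-guided arm will be contacted more, because of endoscopy, the PCR result and regimen selection. The document does not support this. The specimen section {33} takes biopsies and reports resistance for each patient, and these steps come before first-line treatment, well ahead of the UBT. That argument should not be used.

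A reader might also take the attendance gaps as predictions. They are not. The 20% dropout is an overall allowance, not evidence of a gap between arms, and the arithmetic applies to unequal attendance from any cause.

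There are other safeguards. The per-protocol set leaves out untested participants, so a disagreement with ITT could be a warning. It also conditions on good compliance, however, which reminders can affect, so it is only a partial check. Reasons for non-adherence will be reported by group and independent audits are planned. These may reveal a problem, but they do not remove the route.

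**Conclusion.** The point holds as an avoidable bias risk. Unblinded staff book the test, and missing a test is scored as failure, so any arm difference in follow-up effort feeds directly into the ITT and mITT primary outcome. It is neither an error in the plan's figures nor evidence that contact will be unequal.

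The size depends on attendance gaps that the document does not give. On the assumptions shown, a 5-point gap is worth 4.25 points and about an 18% chance of a false finding in that direction; a 10-point gap is worth 8.5 points and about 57%. The change is worth making because it is cheap and the staff are already in place.

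**What to change.** In section {18b}, assign UBT reminders and bookings to the existing blinded data collectors. Start these contacts after that treatment line's 3-day adverse-event and compliance call. Use one schedule timed from the end of therapy, with the same maximum number of attempts in both arms. Keep the rule in {17a} against asking about the regimen. Report UBT attendance and contact attempts by arm. Leave the investigators' clinical contact with participants unrestricted.

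**Cost.** Calls are reassigned and attempts are logged; there is no new visit or test. Collectors must pass clinical questions to the investigators. There is a small added chance that a participant reveals the regimen to a collector. Starting after the 3-day call limits this, because that line's adverse-event and compliance data are then already in. For participants who go on to rescue treatment, a disclosure could still carry over into the next line's call.

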### Data management {19}

Two dedicated investigators will be responsible for data entry and data accuracy by double-checking the data. All data will be entered electronically. The original study forms will provide the option to choose a value from a list of valid codes and a description of what each code means. Checks will be applied at the time of data entry to ensure that the data go into appropriate fields. Participant files are to be stored in numerical order in a secure place. The files will be maintained in storage for a period of 5 years after the completion of the study. Access to the study data will be restricted using a password system.

### Confidentiality {27}

All collected data from this study will be coded using unique patient identifiers so that no individual subjects can be identified. Patient records will be accessed only as per the regulations of the Ethics Committee of the Liaocheng People’s Hospital, and only when necessary. To the extent permitted by applicable laws and regulations, any records relating to participant identification are confidential and will not be made public.

### Plans for collection, laboratory evaluation and storage of biological specimens for genetic or molecular analysis in this trial/future use {33}

The investigators will obtain gastric mucosal biopsy specimens for antimicrobial susceptibility testing. Two biopsy specimens will be obtained from each patient: one from the greater curve of the antrum and one from the lesser curve of the gastric body. The specimens, which are marked with unique patient identifiers, will be kept in only one refrigerator at -28 °C, and maintained by a specimen administrator who will keep the refrigerator key. ShunFeng EXPRESS will transfer the specimens to Zhiyuan Medical Inspection Institute Co., Ltd. (Hangzhou, China) every 3 days using a drikold delivery box. A standard protocol will be used for the biopsy, storage, and transfer processes. The *H. pylori* and genotypic resistance statuses of each patient will be revealed by PCR testing, which will help detect the presence of mutations conferring resistance to clarithromycin and levofloxacin.

## Statistical methods

### Statistical methods for primary and secondary outcomes {20a}

The eradication rate of *H. pylori* will be evaluated using ITT, mITT (including all participants who received at least one dose of the study drug), and per-protocol (PP) analyses (including participants who had good compliance and were re-examined by 13C-UBT). A point estimate and two-sided 95% CI of the difference in eradication rates between the SGT and ET groups will be calculated via the Miettinen & Nurminen method for the primary and secondary outcomes. Participants who have not undergone a re-examined 13C-UBT will be considered as treatment failures, i.e., ‘not eradicated,’ in the statistical analysis. Propensity score analysis will be used to adjust for differences in treatment regimens and potential confounding factors. Compliance and sensitivity analyses will be conducted to compare the treatment responses between compliant and non-compliant participants and determine if there is a significant association between compliance and treatment outcomes. Statistical significance will be set at *P* < 0.05.

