### Intervention description {11a}

The SGT group’s regimens will be selected according to *H. pylori* susceptibility to clarithromycin and levofloxacin. Participants will undergo an upper endoscopy to provide gastric mucosal samples for molecular testing. The test is based on polymerase chain reaction (PCR), which detects *H. pylori* mutations associated with clarithromycin and levofloxacin resistance. The susceptibility testing PCR protocol is outlined in Additional File 1. Regimens for the first-line treatments are based on clarithromycin susceptibility: If the *H. pylori* strain is sensitive to clarithromycin, we will administer clarithromycin triple therapy—esomeprazole (20 mg, twice daily), clarithromycin (500 mg, twice daily), and amoxicillin (1.0 g, twice daily)—for 14 days, as per the recommended guideline [17]. If the strain is clarithromycin resistant, we will administer the HDDT regimen because a network meta-analysis revealed that this treatment is the most optimal first-line therapy for *H. pylori* among the Asian population [24]. If the first-line treatment fails, rescue therapy will be selected according to levofloxacin susceptibility. If the *H. pylori* strain is levofloxacin sensitive, we will administer the levofloxacin quadruple regimen—esomeprazole (20 mg, twice daily), levofloxacin (500 mg, once daily), amoxicillin (1.0 g, twice daily), and colloidal bismuth pectin (150 mg, four times daily)—for 14 days, as per the recommended guideline [17]. If *H. pylori* is levofloxacin-resistant, we will administer the furazolidone quadruple regimen—esomeprazole (20 mg, twice daily), furazolidone (100 mg, twice daily), amoxicillin (1.0 g, twice daily), and colloidal bismuth pectin (150 mg, four times daily)—for 14 days. This furazolidone regimen can provide a satisfactory eradication rate in patients with multiple treatment failures and does not increase the incidence of adverse events [25, 26].

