### Sample size {14}

We will conduct this as an equivalence study, and the calculation of the sample size is based on the primary outcome, which is the first-line eradication rate of *H. pylori*. Using intention-to-treat (ITT) analysis, a meta-analysis comparing SGT vs. BQT as the first-line treatment for *H. pylori* infection found that the pooled eradication rates of SGT and BQT were 86% vs. 78% [12]. A recent meta-analysis reported that the overall eradication rate in patients harbouring susceptible strains was 95.0% (95% CI [94.1–95.9]), but only 63.4% of treatment arms (64/101) achieved good eradication rates (≥ 90%) [14]. Based on these data, our assumption is a 90% eradication rate of susceptibility‐guided sequential strategy, 80% eradication rate of empiric therapy, power of 80%, alpha of 0.05 (two-sided), and allocation ratio of 1:1. The calculated sample size is 197 participants per arm. Considering a dropout rate of 20%, we have to recruit at least 494 patients (247 participants per arm) for the study. Therefore, we aim to recruit 500 participants for this study.

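### The planned between-arm test of the rescue eradication rate compares first-line failures only, so it is not a randomised comparison and its bias has unknown sign and size

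*Protocol article*

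**What the plan says.** Outcomes {12} names as secondary outcomes "The rescue treatment and the overall eradication rates in the SGT and ET groups". The rescue rate is thus an outcome in its own right, separate from the overall (first-line plus rescue) rate.

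Statistical methods {20a} prescribes one analysis for the primary and secondary outcomes together: "A point estimate and two-sided 95% CI of the difference in eradication rates between the SGT and ET groups will be calculated" by the Miettinen-Nurminen method, with a 0.05 significance level. No secondary outcome is exempted or labelled descriptive. The section also mentions a propensity score analysis for regimen differences and confounders, without linking it to a particular outcome.

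Entry to rescue depends on the first-line result in both arms. For SGT, Intervention description {11a} says: "If the first-line treatment fails, rescue therapy will be selected according to levofloxacin susceptibility". For ET, Explanation for the choice of comparators {6b} gives high-dose dual therapy when bismuth quadruple therapy fails. First-line treatment is bismuth quadruple therapy for everyone in ET. In SGT it is clarithromycin triple or high-dose dual therapy, depending on clarithromycin susceptibility.

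Allocation happens once, after consent (Implementation {16c}). The article describes no second randomisation at rescue.

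**The concern.** A rescue eradication rate has first-line failures as its denominator. Failure occurs after randomisation and depends on the first-line regimen, which is what was randomised. The SGT and ET rescue groups are therefore not two random samples of the same population. They can differ in size and in how hard the infection is to cure.

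The rescue regimens also differ by arm, so the planned difference mixes two things that it cannot separate: any real difference between rescue regimens, and the difference in who was left to be rescued. An interval and P value attached to that mixture look like a treatment comparison but do not estimate one. This matters because the trial studies a strategy that guides both lines of treatment, and the rescue contrast has the same inferential standing in {20a} as the overall rate, which does keep the randomised comparison.

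This is a different contrast from the high-dose dual therapy subgroup comparison in Methods for additional analyses {20b}.

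**Working it through.** **1. The plan's own figure.** Sample size {14} states "our assumption is a 90% eradication rate of" the guided strategy and "80% eradication rate of empiric therapy, power of 80%, alpha of 0.05 (two-sided), and allocation ratio of 1:1". With unpooled variance:

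n = (1.960 + 0.842)² × (0.9×0.1 + 0.8×0.2) / 0.10² = 196.2, rounded up to 197 per arm.

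This matches "The calculated sample size is 197 participants per arm". For 20% dropout, 197/0.8 = 246.25, so 247 per arm and 494 in total, also as stated. The target is 500, about 250 per arm. No sample-size figure is in dispute.

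**2. Size of the rescue groups.**
- 250 per arm: 250 × 0.10 = 25 SGT failures; 250 × 0.20 = 50 ET failures.
- 20% dropout, 200 evaluable per arm: 20 and 40.

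For scale, if the observed rescue rate were 70% in both groups of 25 and 50, the Miettinen-Nurminen 95% CI for the difference would run from about -23 to +21 points.

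**3. How selection enters.** Suppose rescue is equally effective in both arms within patient type: 90% in ordinary cases and r in hard-to-treat cases. Let s be the share of hard cases among an arm's first-line failures. Then

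rescue difference (SGT - ET) = -(s_SGT - s_ET) × (0.90 - r).

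The true within-type effect is zero, so any non-zero value is selection. Its sign depends on which arm has the larger share of hard cases, and the documents say nothing about that.

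**4. Illustration.** The documents give no rescue rates and no hard-to-treat share, so these are assumptions. Let a fraction h of all participants be hard to treat and fail any first-line regimen. Then s_SGT = h/0.10 and s_ET = h/0.20, and the difference is -5h × (0.90 - r). Significance was simulated with 250 per arm, using a score test with the Miettinen-Nurminen variance factor.

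| Cure in hard cases, r | h | Rescue SGT vs ET | Difference (points) | Trials with P < 0.05 |
|---|---|---|---|---|
| 30% | 2% | 78% vs 84% | -6 | about 11% |
| 30% | 4% | 66% vs 78% | -12 | about 21% |
| 30% | 8% | 42% vs 66% | -24 | about 51% |
| 50% | 2% | 82% vs 86% | -4 | about 8% |
| 50% | 4% | 74% vs 82% | -8 | about 13% |
| 50% | 8% | 58% vs 74% | -16 | about 29% |
| 70% | 2% | 86% vs 88% | -2 | about 6% |
| 70% | 4% | 82% vs 86% | -4 | about 8% |
| 70% | 8% | 74% vs 82% | -8 | about 13% |

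With 200 evaluable per arm, the r = 30% figures fall to about 18% at h = 4% and 42% at h = 8%.

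**5. The overall rate in the same model.** SGT: 0.90 + 0.10 × rescue rate = 0.99 - h(0.90 - r). ET: 0.80 + 0.20 × rescue rate = 0.98 - h(0.90 - r). The difference is +1 point in every row. For example, at r = 30% and h = 8% it is 94.2% vs 93.2%. The rescue contrast ranks the arms the other way in every row.

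**The case against.** Several points on the other side carry weight.

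- **The plan mentions adjustment.** The propensity score sentence in {20a} could be read as covering this. It is not tied to the rescue contrast, and a propensity score balances measured covariates only. How hard an infection is to cure is largely unmeasured, and the rescue regimen is fixed by arm (and by susceptibility within SGT). It does not restore comparability.
- **The valid comparison is already there.** The overall rate is a planned secondary outcome, and its intention-to-treat analysis preserves randomisation. This stands. It narrows the point to the status given to one further secondary rate.
- **The magnitude is assumed.** This stands too. At 70% cure in hard cases forming 2% of participants, the distortion is 2 points and rejection is near nominal; the large figures need both a low cure rate and a sizeable hard group.
- **An analysis plan could add the label.** It could, but the concern is not a missing detail: {20a} itself prescribes the difference and the significance level for this outcome.

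A reader might go further and infer that SGT's remaining failures must be the harder cases, so that the contrast is bound to disfavour SGT. The documents do not support that. The negative sign in the illustration comes from assuming that the extra ET failures are easier to cure. The first-line regimens differ in kind, so the two sets of failures need not be nested, and the bias could run either way. Nor do the documents state a rescue-specific hypothesis; the hypothesis in Background and rationale {6a} concerns the whole strategy.

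**Conclusion.** The concern holds in a limited form. The article plans an inferential SGT-minus-ET comparison of rescue eradication in groups formed by a post-randomisation outcome that treatment affects: about 25 vs 50 participants at the planned rates, or about 20 vs 40 with 20% dropout. It is not a randomised comparison, and the sign and size of its bias are unknown. That conclusion rests only on the stated design.

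The range of -2 to -24 points, with 6% to 51% of trials significant, rests on assumed rescue rates and an assumed hard-to-treat share. It shows what selection could do and does not predict what it will do. The primary first-line outcome and the overall rate are not affected, and the point should not be read as casting doubt on either.

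**What to change.** In Outcomes {12} and Statistical methods {20a}:

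- Report the rescue eradication rate within each arm, and by rescue regimen, each with its own 95% CI. Label it descriptive and non-randomised, with no between-arm P value and no efficacy claim. If a difference is still shown, mark it exploratory.
- State that the overall (first-line plus rescue) eradication rate in all randomised participants is the only inferential between-arm comparison that includes rescue.

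The cost is a change of wording and the loss of one between-arm secondary test. It needs no new data, no change to the sample size and no change to treatment.

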### Criteria for discontinuing or modifying allocated interventions {11b}

The safety of *H. pylori* eradication treatments is well defined, where taste disturbance, diarrhoea, nausea, and abdominal pain are the most frequent adverse events (AEs). The majority of AEs are mild and temporary. It is estimated that only 1.3% of patients discontinue treatment due to AEs [27]. In our study, when participants report AEs, they will be evaluated by the investigators. The study drugs may be discontinued for any of the following reasons: participants experience severe AEs, are declared unsuitable for continued drug use, or cannot comply with the study procedures. Participants may withdraw from the study for any reason at any time. The reasons for withdrawal will be recorded if disclosed by the participants.

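### Days of drug taken are cut only at 10, so the compliance analysis cannot show whether 10–13-day takers, all kept in the per-protocol set, did as well as 14-day takers, and its significance verdict could mislead in either direction

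*Protocol article*

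**What the plan says.** All statements are in the protocol article.

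- **What is recorded** (Plans for assessment and collection of outcomes {18a}): "Study drug compliance will be based on the number of days of drug administration".
- **How it is cut** (same section): "10 or more days will be considered good compliance and less than 10 days bad compliance". The reason given is outside evidence that 10-day regimens perform well. The Discussion repeats 10 to 14 days as a single compliant class. It also notes that the usual definition asks for more than 80% of the drug.
- **Where the cut is used** (Statistical methods for primary and secondary outcomes {20a}): good compliance, together with a repeat breath test, defines the per-protocol set. The same section plans to "compare the treatment responses between compliant and non-compliant participants and determine if there is a significant association between compliance and treatment outcomes", with significance at P < 0.05. Sensitivity analyses are named in that sentence but not described.
- **Missing outcomes** ({20a} and {20c}): a participant without a repeat breath test counts as not eradicated.
- **Expected non-compliance**: no figure is given for participants under 10 days. The nearest is in {11b}: "It is estimated that only 1.3% of patients discontinue treatment due to AEs".

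**The concern.** Every regimen in {6b} and {11a} is prescribed for 14 days. A participant who stops after day 10 has taken 71% of the course and is still per-protocol. Whether such participants do as well as full-course takers bears directly on what the per-protocol result means. The trial will hold the data to look at this, but the stated split removes the contrast.

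The contrast that is left, 10 or more days against fewer, ends in a verdict on significance. If few participants stop before day 10, a non-significant result carries little information, yet a reader could take it to mean that compliance does not matter or that the 10-day cut is sound. If early stoppers also skip the breath test, the missing-as-failure rule can yield a significant result that reflects missing tests and not drug exposure. At stake is the reading of the per-protocol and compliance analyses only.

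**Working it through.** **1. The plan's own figures.** The article gives no figure for the compliance analysis. Its sample size reproduces for 90% vs 80%, two-sided 0.05 and 80% power: (1.96 + 0.8416)² × (0.90×0.10 + 0.80×0.20) / 0.10² = 196.2, so 197 per arm, as stated ("The calculated sample size is 197 participants per arm"). With 20% dropout, 197 / 0.80 = 246.25, so 247. The calculations below use N = 500 and a reference eradication rate of 85%, the midpoint of the two planned rates.

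**2. What the cut does.** 10/14 = 71.4%. The usual threshold cited in the Discussion is 0.80 × 14 = 11.2 days, so more than 80% means 12 or more whole days (11/14 = 78.6%, 12/14 = 85.7%). Participants at 10 and 11 days are compliant here but would not be under that definition. A comparison of 10 or more with under 10 days holds all 10–13-day takers on one side, so it cannot estimate 10–13 vs 14 at any sample size.

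**3. Precision of the planned contrast.** Let m be the number under 10 days. The only anchor is 0.013 × 500 = 6.5, about 7, and it covers stopping for adverse events only. The range of m and the 70% rate are assumptions.

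SE = √(0.85×0.15/(500−m) + 0.70×0.30/m); half-width = 1.96 × SE; power = Φ(0.15/SE − 1.96).

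| m | SE | 95% CI half-width | Power |
|---|---|---|---|
| 7 | 0.174 | 34 points | 14% |
| 15 | 0.119 | 23 points | 24% |
| 25 | 0.093 | 18 points | 36% |
| 50 | 0.067 | 13 points | 61% |

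An exact Fisher calculation for a 20-point gap (85% vs 65%) gives power of 24% with 6 non-compliers, 48% with 15, 65% with 25 and 89% with 50. The answer turns on a share that the article does not fix.

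**4. Effect of counting a missing test as failure.** Suppose eradication is truly 85% in both compliance groups, and 40% of early stoppers but 10% of the others miss the breath test (assumed shares). The analysed rates are 0.85 × 0.60 = 51.0% and 0.85 × 0.90 = 76.5%, a 25.5-point gap with no effect of compliance. If instead the true rates are 70% and 85%, the analysed rates are 42.0% and 76.5%. With m = 15 the power then rises from 24% to about 76%: SE = √(0.765×0.235/485 + 0.42×0.58/15) = 0.129, and Φ(0.345/0.129 − 1.96) ≈ 0.76.

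**5. Precision of 10–13 vs 14 days.** Take k participants at 10–13 days, treat the rest of the 500 as 14-day takers, and set both rates at 85%. The half-width 1.96 × √(0.85×0.15×(1/k + 1/(500−k))) is 18, 14 and 10 points for k = 15, 25 and 50. That supports an estimate with an interval, not a test.

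**6. Arm.** With assumed compliance of 95% (susceptibility-guided) and 85% (empirical), eradication of 90% and 80%, and no effect of compliance within either arm, an unadjusted pooled comparison gives (0.95×0.90 + 0.85×0.80)/1.80 = 85.3% against (0.05×0.90 + 0.15×0.80)/0.20 = 82.5%. The spurious 2.8 points compare with a half-width of about 11 points in that case (450 vs 50 participants).

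**The case against.** The plan can be defended on several counts, and most of them limit the point without removing it.

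- **The 10-day claim.** A reader might infer that the plan assumes 10 days to be as good as 14. It does not: {18a} and the Discussion claim only that 10 days gives a good or satisfactory rate. This stands.
- **Purpose.** Nothing in {20a} presents the compliance analysis as a check of the cut. This also stands. What remains is that the cut decides per-protocol membership and no stated analysis looks inside the 10–14-day class.
- **A near-certain null.** A reader might infer that non-significance is almost guaranteed. The documents do not support that. The 1.3% omits stopping for other reasons, power is 61% with 50 early stoppers even on the assumed 15-point gap, and the missing-as-failure rule can push the result the other way.
- **Pooling over arms.** The article does not say the comparison is unadjusted, and a propensity score analysis is planned, though not tied to this comparison. The illustrated bias is small. Adjusting for arm is good practice and a minor matter here.
- **Detail left to the analysis plan.** Model form and the content of the sensitivity analyses may well be settled there. The binary cut, its two uses and the significance verdict, however, are stated in the article.
- **The alternative is weak too.** The 10–13 vs 14-day contrast is non-randomised and imprecise. This is true, and is why it should be reported as an estimate.

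**Conclusion.** The point holds as a minor improvement to a supportive analysis. It is certain from the text that the single cut at 10 days hides any difference between 10–13-day and 14-day takers, both in the compliance analysis and in the per-protocol set. It depends on assumptions that the remaining test is weak: power is about 14% to 61% for 7 to 50 early stoppers of 500 at 70% vs 85%. It depends equally on assumptions that missing tests counted as failures create an association: 25.5 points with 40% vs 10% missing and no true effect. Since the error could run either way, neither a significant nor a non-significant result would be a sound verdict on compliance or on the cut. The intention-to-treat and modified intention-to-treat results are not affected.

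**What to change.** In {20a}, replace the two-group significance test with the following, for the first-line course:

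1. Tabulate eradication with 95% CIs for under 10, 10–13 and 14 days, by arm.
2. Assess the association with days taken as an ordered variable in a logistic model that includes arm. Run it twice: with a missing breath test as failure, and among participants with a test result.
3. Add a per-protocol sensitivity analysis with a stricter cut, for example more than 80% of the course, the definition cited in the Discussion.
4. State that all of this is descriptive, and that a non-significant association will not be read as support for the 10-day cut.

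The cost is a few lines of analysis text and one extra table. Days taken are already recorded, so no new data are needed, and the sample size and primary analysis do not change.
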